
**Fig. 1 Fig1:**
[figure not shown]
CONSORT diagram of participant flow through the study

### Delivery of the intervention

The massages will be provided by a team of massage therapists with experience in pregnancy massage and perinatal loss across multiple sites within Australia. Massage therapists will be recruited (1) through the study personnel who have previously worked with the therapists and or (2) through an expression of interest via a pregnancy massage training organisation in Australia. Therapists from all states and territories across Australia who had completed pregnancy massage training post-completion of their initial massage qualifications are able to express an interest in being study massage therapists. At least 20 massage therapists will be recruited to ensure that there are therapists in differing states and territories across Australia due to the difficulty of recruiting 75 people from a more limited geographic area. The exact number of therapists to be recruited is unknown as it is undetermined how many therapists will express an interest. The massage therapists attend an online 3-h training on the massage study intervention and facilitation of the massage experience for individuals pregnant after a loss as well as training on grief and resources available to individuals pregnant after a loss prior to becoming study massage therapists. The massage treatments are administered in the massage clinician’s office and follow a protocol that allows for treatment to be tailored for each participant depending on the presentation on the day. See Additional file 1 for massage protocol. The focus of each treatment is determined by the participant via the Measure Yourself Concerns and Wellbeing (MYCaW) patient-reported outcome measure (PROM) (46), and the massage therapist administers remedial and or relaxation massage techniques.

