### Sample size

The study aims to recruit a total of 75 pregnant people meeting the study criteria. This feasibility study is not expecting large effect sizes as anxiety and depression experienced during a pregnancy after stillbirth do not decrease until 6 months post birth (42). Thus, it is hypothesized that while the immediate effects of the massage intervention might be larger, the long-term effects will likely be small (< 0.1). Using the approach by Whitehead et al. for small effect sizes (43), it is estimated a minimum of 50 pregnant people is needed to reliably detect a small effect size (< 0.1). A sample of 75 pregnant women allows for a 10–15% drop out rate and 10% for whom data is incomplete.

A sub-group sample of 20 participants will be invited via purposive sampling to participate in the qualitative phase of the mixed-methods design. Twenty participants have been proposed as optimal to ‘improve open and frank exchange of information and mitigate some of the bias and validity concerns inherent in qualitative research’ (44). Purposive sampling will consider the type of loss (stillbirth and TFMR), early stillbirth/TMFR loss (losses between 20 and 29 + 6 weeks of gestation) and late stillbirth/TMFR loss (losses between 30 and birth).

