### Intervention

Each participant will have access to up to 5 allocated 60-min massage consultations see Fig. 1. The massage treatments will be administered within a 4-month period at intervals of participant and therapist dyad determining based on participant preference and therapist treatment planning. Each massage consultation will be individualised to meet the needs of the participant on the day of treatment. The conceptual approach utilized is based on a vulnerability-to-stress concept. The vulnerability-to-stress concept acknowledges the impact of stress on vulnerability and recognises protective factors that can help reduce stress (45). For women pregnant after a stillbirth, the vulnerability is the previous loss (and any other pregnancy losses) as well as any biological factors, and the stress is being pregnant again (and the fear of another loss). We are proposing that massage might be a protective factor to help manage stress. This conceptual approach was used in a published case study (36). The massage aims to support women by addressing altered psycho-behavioural and physiological factors associated with vulnerability and stress such as countering feelings of loss of control via allowing participants to individualise their treatments (e.g. depth, area of the body to be treated, what they want to be treated). See Additional file 1 for the protocol for the massage which covers more in-depth how massage may do this. The massage intervention uses hands-on techniques, listening and creating the environment to build a therapeutic alliance to help provide protective factors and manage the stress of pregnancy after a stillbirth. Allowable massage strokes for therapist incorporation into treatment to address the study aims include longitudinal gliding, transverse gliding, digital ischemic pressure, transverse frictions and transverse gliding. The use of these massage strokes is based on prior pregnancy massage research (39, 42). The areas of the body treated, the depth of treatment and which massage strokes used will be determined by the massage therapist reflecting real-world clinical massage practice. No other form of massage therapy or hands-on modalities (e.g. reflexology, aromatherapy massage) are to be used and nor are other healing modalities (e.g. reiki). Treatment sessions are 60 min and include hands-on treatment time as well as the time prior and after the hands-on massage to consult with the participant about their treatment and plan the timing for the next treatment session. See Additional file 1.

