## Data analysis

### Analysis of quantitative data

The participant’s demographic and clinical characteristics will be summarised using descriptive statistics. Summary statistics of the observational clinical treatment data (e.g. worry, anxiety, etc.) will be reported and an appropriate matched test will be used to determine significant differences between baseline and post-final treatment scores (e.g. paired *t*-test if data are normally distributed, Wilcoxon matched-pairs test if not).

Three treatment effect modifiers have been identified: (1) the amount of other support services utilised, (2) passing the gestational age during the study intervention that they experienced their stillbirth, (3) the time between the stillbirth and this pregnancy, and (4) the number of study intervention treatments received. The correlational analysis will be used to determine associations between observational treatment outcomes and support services utilized (e.g. talk therapy (psychology/counselling), peer support etc.). Appropriate comparative tests will be used to determine whether there is a relationship between observed treatment outcomes and gestation of stillbirth, the duration of the interpregnancy interval, and the number of treatments administered.

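### The planned before-after tests take no account of therapist; if change scores correlate within therapist, the secondary p-values will be somewhat too small

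*Protocol article*

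**What the plan says.** Sample size (protocol article): "The study aims to recruit a total of 75 pregnant people meeting the study criteria", and "A sample of 75 pregnant women allows for a 10–15% drop out rate and 10% for whom data is incomplete".

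Delivery of the intervention: "At least 20 massage therapists will be recruited", spread over the Australian states and territories, each working in their own clinic. No upper number is set: "The exact number of therapists to be recruited is unknown as it is undetermined how many therapists will express an interest".

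Intervention: the therapist has discretion over area and depth, and "which massage strokes used will be determined by the massage therapist". Listening, the treatment environment and the building of a therapeutic alliance are presented as parts of the intervention. Timing is settled between the participant and the therapist as a dyad.

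Analysis of quantitative data: "an appropriate matched test will be used to determine significant differences between baseline and post-final treatment scores". The paired t-test and the Wilcoxon matched-pairs test are given as examples. Neither this section nor the sample size section mentions therapist.

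**The concern.** A matched test deals with one kind of dependence, that between the two scores of the same woman. It reduces each woman to a change score and then treats those changes as independent. Here the women are grouped by therapist, and the article gives reasons why women of the same therapist might respond alike: one practitioner's technique, one clinic, one manner of building the alliance. If they do, 56 women carry less information than 56 independent women, and the test overstates the evidence for change.

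What is at stake is limited. The plan sets out to identify significant changes on several secondary scales, and those p-values may be cited in support of a larger trial. That trial would also have to consider between-therapist variation in its sample size, and neither named test gives an estimate of it.

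**Working it through.** **Inputs from the article.** 75 women recruited; at least 20 therapists; 10–15% dropout plus 10% incomplete data.

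**Assumptions.** ICC of the change scores 0.01 to 0.10; coefficient of variation (CV) of therapist caseload 0 (equal) or 0.7 (uneven); two-sided 5% level; one therapist per woman throughout, which the dyad wording suggests. The article gives none of these as figures.

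**Number analysed.** Subtracting the larger losses together leaves 75 × (1 − 0.25) = 56. Applying the smaller losses in sequence leaves 75 × 0.90 × 0.90 = 61. I use 56. Going the other way, the stated minimum of 50 inflates to 50/0.80 = 63 or 50/0.75 = 67, so 75 more than covers it. How the 50 was obtained is a separate question on which this point does not depend.

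**Caseload.** m = 56/20 = 2.8 women analysed per therapist (75/20 = 3.75 if nobody is lost).

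**Formulas.**
- Design effect: DE = 1 + ((1 + CV²) × m − 1) × ICC.
- True standard error relative to the unclustered one: √DE.
- True two-sided error: 2 × (1 − Φ(1.96/√DE)).

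Worked example, ICC 0.05 and equal caseloads: DE = 1 + (2.8 − 1) × 0.05 = 1.09; √1.09 = 1.044; 1.96/1.044 = 1.877; error 0.0605.

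20 therapists, 56 women analysed:

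| ICC | Equal caseloads: DE, √DE, error | CV 0.7: DE, √DE, error | Simulated error, random allocation |
|---|---|---|---|
| 0.01 | 1.018, 1.009, 0.0521 | 1.032, 1.016, 0.0537 | 0.0510 |
| 0.05 | 1.090, 1.044, 0.0605 | 1.159, 1.076, 0.0686 | 0.0659 |
| 0.10 | 1.180, 1.086, 0.0712 | 1.317, 1.148, 0.0877 | 0.0817 |

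The last column comes from simulating the paired t-test with women allocated at random to 20 therapists, 40,000 runs per setting. With an ICC of zero it gave 0.052, so the test holds its level when therapists do not differ.

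**Sensitivity.**
- 30 therapists, 56 analysed, equal caseloads: error 0.051, 0.055 and 0.060 at ICC 0.01, 0.05 and 0.10.
- 20 therapists, all 75 analysed, equal caseloads: 0.053, 0.066 and 0.083 (simulated with random allocation: 0.055, 0.072 and 0.093).

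The formulas describe the t-test. The Wilcoxon test also assumes independent women, but I did not compute its error separately.

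**Precision of an estimated ICC.** With k = 20 therapists, m = 3 and ICC 0.05, the large-sample standard error is √[2 × (1 − ICC)² × (1 + (m − 1) × ICC)² / (m × (m − 1) × (k − 1))] = √[2 × 0.9025 × 1.21 / 114] = 0.14. A 95% interval therefore runs from zero to about 0.3.

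**The case against.** Several points on the other side stand.

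- The tests are given as examples of an appropriate matched test, so the plan does not strictly fix them. The article condenses a fuller plan that is not shown, and that plan may include a therapist term. This is why the point is an inexpensive improvement and not a complaint about missing detail: followed as written, the named tests would understate the standard error if therapists differ.
- The case for similarity within therapist is not one-sided. Participants set the focus of each session and can choose depth and area, and all therapists have the same study training and follow one massage protocol. The ICC could be close to zero, and then the tests are sound.
- The scales are secondary outcomes in a single-arm feasibility trial. The progression criteria rest on recruitment, retention, the percentage who feel supported and a qualitative judgement, and none uses a matched-test p-value.
- An ICC from about three women per therapist will be imprecise, and its estimate may well be zero.

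A reader might infer more than the documents support:

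- **That the p-values are too small as a matter of fact.** That depends on an ICC the article does not give.
- **That the true error reaches 14%.** This takes an ICC of 0.15, a caseload CV of 0.8 and all 75 women analysed: DE = 1 + (1.64 × 3.75 − 1) × 0.15 = 1.77, error 0.14. Zero loss contradicts the article's own allowance for dropout and incomplete data.
- **That intervals for the CARE empathy score or the supportive percentage will be too narrow.** The article plans no such intervals; the point applies only if they are reported.
- **That an effective sample below 50 breaches the stated minimum.** At a standardised effect of 0.1, 50 women give a paired test only about 11% power, so falling below 50 shows no particular harm from clustering.

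**Conclusion.** The point holds in conditional form. The named tests treat women as independent although the design groups them within therapists. If change scores correlate within therapist, the standard errors and p-values of the secondary before-after comparisons will be too small. With 20 therapists and 56 women analysed, the unclustered standard error is about 1–8% too small for ICCs of 0.01 to 0.10 with equal caseloads, and up to 13% too small at a caseload CV of 0.7 (1 − 1/1.148). The true error of a nominal 5% test is then about 5% at ICC 0.01, 6–7% at 0.05 and 7–9% at 0.10. More therapists reduce it, and an ICC of zero removes it. The ICC, the caseload spread and the 5% level are assumptions. The primary outcomes and the progression decision are unaffected. This is a modest improvement to secondary analyses.

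**What to change.** In the quantitative analysis section, state that change scores will be analysed with a random intercept for therapist, or with a therapist-cluster-robust standard error and a small-sample correction, at least as a sensitivity analysis beside the matched test. Apply the same clustering to any interval reported for the CARE score or the supportive percentage. Report the number of therapists, the caseload distribution and the therapist ICC with its interval, labelled as descriptive planning information. If an unpublished analysis plan already does this, a pointer to it is enough.

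The cost is a sentence or two of wording. The trial already knows who treated whom, so recruitment, visits and questionnaires do not change. The price is slightly wider intervals and an ICC too imprecise to fix a later sample size by itself.

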### Side effects

Participants will be sent a questionnaire 24 to 48 h after each massage treatment asking about experienced side-effects from the massage treatment such as post-massage soreness, headaches, tiredness or any other side effects (please specify). These side effects are based on research into side effects, massage and pregnancy (47). Adverse events are recorded and reported quarterly to the Research Ethics Committee, and serious adverse events are required to be reported immediately (Additional file 2).

### Criteria for discontinuing the intervention

The intervention will cease if participants are advised by their obstetric healthcare providers (i.e. on bed rest), if they are no longer pregnant or if the study participant delivers their baby prior to completing the allocated study intervention.

### Assessments

The measures used to provide data to meet the three objectives of the study are as follows:

#### Trial data

Data will be collected by the study team throughout the trial on the number of inquiries, number of participants, drop-out rates and compliance with completing the validated outcome measures. See Table 2.

**Table 2 Tab2:** Outcome measures and timing

Project outcome	Measured by^a^	Timepoint				
*To assess the feasibility and acceptability of the massage intervention including intervention delivery and outcome measure compliance*						
		At enrolment	Post recruitment completion	*Study intervention*	Post-study intervention completion	At end of the study
				At each study treatment visit		
Feasibility	Number of enquiries		✓			
	Recruitment rates					✓
	Retention rates					✓
	Compliance with completing the outcome measures					✓
Acceptability						✓
○ Acceptability of the study processes	Retention rates					✓
	Response quality/compliance with the validated outcome measures					
	Post-intervention qualitative questionnaire				✓	
	In-depth interviews with study participants				✓	
○ Acceptability of the study intervention (massage)	Study completion rates					✓
	Consultation and Relational Empathy (CARE) PREM (47)				✓	
	Measure Yourself Concerns and Wellbeing (MYCaW) PROM (40)			✓		
	Post-intervention qualitative questionnaire				✓	
	In-depth interviews with study participants				✓	
	Response quality/compliance with the validated outcome measures					✓
*To determine the optimal timing of therapy, measures of anxiety, worry, stress and self-management. Including intervention delivery and outcome measure compliance*						
Timing (Treatment utilisation)	Collecting data (dates) of when study participants utilised their massages				✓	
Anxiety	Generalized Anxiety Disorder Assessment (GAD-7) (43)	✓			✓	
Worry	Cambridge Worry Score (41)	✓			✓	
Stress	Perceived Stress Scale (46)	✓			✓	
Self-management	Revised Prenatal Coping Inventory (44) Strategies Used by People to Promote Health measure (45)	✓ ✓			✓	
*To conduct a thematic analysis of experiences of women undertaking the intervention to assess acceptability of the study and the intervention*						
Experience of the study intervention and study processes	Post-intervention qualitative questionnaire Consultation and Relational Empathy (CARE) PREM (47) In-depth interviews with study participants Measure Yourself Concerns and Wellbeing (MYCaW) PROM (40)				✓	
					✓	
					✓	
				✓		

^a^The measures used in this study may provide data for multiple project outcomes. “At the end of the study” is after the final participant has completed the intervention and completed the final post-study intervention questionnaires

#### Treatment utilisation

This data will describe when study participants utilised their massages (massage timing) to inform hypothesis generation regarding dosing value.

#### Validated self-reported questionnaires

Worry, anxiety, coping, self-efficacy, stress and empathy will be assessed in the study via the following questionnaires:oWorry will be assessed via the *Cambridge Worry Score* (48) which is 17-item instrument that measures the content and extent of worries in pregnancy (48, 49). The total score range is from ‘zero to 85 with a higher score representing greater severity of worries’ (48).oMaternal anxiety symptoms will be assessed *using the Generalized Anxiety Disorder Assessment (GAD-7)* (50) which is a 7-item instrument that measures the severity of generalised anxiety disorder. The total score range is from zero to 21 with scores of 5–9 representing mild anxiety, 10–14 moderate anxiety and 15–21 representing severe anxiety (50)*.*oCoping via* the self-reported Revised Prenatal Coping Inventory (NuPCI)* (51) will be assessed. This scale has 32 items that evaluate the coping strategies of pregnant (51). The NuPCI consists of 3 subscales: positive attitude (15 items), avoidance (11 items) and spiritual-positive coping (6 items) (51). A higher score indicates more frequent use of a specific coping strategy (51).oSelf-efficacy via the *Strategies Used by People to Promote Health measure (SUPPH-29)* (52) will be assessed. This scale has 29 items that measure self-care self-efficacy (52). The SUPPH-29 consists of 3 sub-scales positive attitude (16 items), stress reduction (10 items) and decision making (3 items) (52). The total score range is from 29 to 145 with a higher score indicating greater self-confidence to carry out self-care strategies (52).oMaternal stress symptoms via the *Perceived Stress Scale* (PSS) (53) will be assessed. The scale has 10 items that measure perceived personal stress (53). The total score range is from zero to 40 with a score ranging from 0 to 13 considered low stress, 14–26 moderate stress and 27–40 high stress (53).oEmpathy in the context of the therapeutic relationship via the *Consultation and Relational Empathy (CARE) patient-reported experience measure (PREM)* (54). This scale has 10 items that measures patients’ perceptions of relational empathy in the consultation (54). The total score range is from 10 to 40 with higher scores indicating greater perceived relational empathy (54).o*Measure Yourself Concerns and Wellbeing (MYCaW)* assesses patient-reported outcomes *(PROM)* (46). This measure has the space for participants to write down two concerns they want help with, and then, the concerns are rated for severity using a 6-point Likert scale ranging from ‘not bothering me at all (0)’ to ‘bothers me greatly (6)’. A person’s wellbeing is also rated using the same 6-point Likert scale. There are two open-ended questions that ask if anything else important is happening in the person’s life and what has been most important about the treatment they received.

Researchers in the iCHOOSE Study are developing a core outcome set for stillbirth care research (55, 56), and this will guide future outcome measures for stillbirth research. The validated self-reported questionnaires evaluating worry and anxiety have been used together in previous research as outcome measures in stillbirth research (57) and influenced our use of these outcome measures. Worry, anxiety and stress have ‘intertwined behavioural and neural underpinnings’ (58); however, they have important unique characteristics that impact the way that they are experienced. Evaluating worry, stress and anxiety allows the researchers to capture the potential varied psychological states that can occur throughout a pregnancy after stillbirth especially when milestone events are passed without bad news/harm (e.g. gestation of previous loss, genetic and or anomaly scans).

*A post-intervention qualitative questionnaire* designed by the study researchers was based on a questionnaire used in previous stillbirth and massage research (36) (see Additional file 4) and assesses treatment utilisation and acceptability (Q.A-D), the appropriateness and suitability of the validated outcome measures the study used (Q.E), participant’s views of the study benefits (Q.G-L) and the participants’ perception of the study intervention to be a support for pregnant individuals via a massage intervention (Q.M).

An *in-depth interview* is intended to collect rich descriptions of participant experiences of massage and identify important aspects of care as well as provide information on the acceptability of the study intervention. Twenty study participants will be interviewed using a semi-structured approach by the study PI. The interviews will be conducted online via Zoom, recorded and transcribed verbatim by Cockatoo AI transcription services (59).

#### Data collection

Some women may give birth before receiving their allocated treatments. Intervention delivery and data collection will cease for participants who give birth prior to completing the full study protocol, and collected data will be kept within the data set. Attempts will be made to collect the final quantitative and qualitative data from participants who fall into this category. The inclusion criteria for participants to be no more than 30 weeks of gestation (Table 1) are in place to minimise participants giving birth prior to completing the full study protocol. Participants who give birth prior to completing the full study protocol will be emailed inviting them to complete the post-intervention online questionnaires and informing them that they are able to participate in the in-depth interview (if applicable) if they desire. A follow-up email will be sent 2 weeks after the first email.

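### Women may complete the final questionnaires after birth, and the single pre-post test does not separate these scores, although two of the scales concern pregnancy itself

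*Protocol article*

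**What the plan says.** The Data collection section expects some women to deliver before their massages are finished. It states that "Intervention delivery and data collection will cease for participants who give birth prior to completing the full study protocol", and that "collected data will be kept within the data set". The next sentence reads: "Attempts will be made to collect the final quantitative and qualitative data from participants who fall into this category". These women "will be emailed inviting them to complete the post-intervention online questionnaires", and "A follow-up email will be sent 2 weeks after the first email". The first email is not dated, no maximum time since birth is set, and no postnatal version of any instrument is named.

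Table 2 places the worry, anxiety, stress and self-management measures at enrolment and again when the intervention is complete. I read its self-management row as covering both NuPCI and SUPPH-29, in line with the Method section, which has outcome measures completed before and after the intervention.

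The Cambridge Worry Score is described as an instrument that "measures the content and extent of worries in pregnancy". NuPCI is described as a prenatal inventory of pregnant women's coping strategies. GAD-7, PSS and SUPPH-29 are described without reference to pregnancy.

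Under Analysis of quantitative data, "an appropriate matched test will be used to determine significant differences between baseline and post-final treatment scores". The section makes no distinction by pregnancy status at the final questionnaire, and having given birth is not among the listed effect modifiers.

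**The concern.** A woman who answers a pregnancy worry scale or a prenatal coping inventory after delivery is not reporting the quantity she reported at baseline. Her paired difference mixes any change over the course of massage with the change from being pregnant to not being pregnant. The study has no comparison group, so nothing in the data separates the two.

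For anxiety, stress and self-efficacy the construct still applies after birth, but birth may move the score. The Intervention section itself names the new pregnancy and the fear of another loss as the stressor. A live birth removes that stressor and another loss realises the fear, so the shift could go either way.

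The planned comparison of outcomes with the number of treatments has the same weakness. Women who deliver before finishing have had fewer massages and are also the ones who give post-birth scores.

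What is at stake is the interpretation of the secondary pre-post changes as preliminary evidence, not the feasibility decision.

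**Working it through.** **1. Do post-birth scores reach the test?** Three statements have to be joined. Final quantitative data are sought after birth (Data collection). The scales belong to the post-intervention set (Table 2). One matched test uses the baseline and final scores (Analysis of quantitative data). Nothing stated takes the post-birth scores out. Pooling therefore follows from the text, though no sentence says it.

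**2. Can finals fall after birth?** Inputs from Table 1: entry below 30 weeks and a window of 4 months.
- Window: 4 × 365.25 / 12 / 7 = 17.4 weeks.
- Latest end of window: 30 + 17.4 = about 47 weeks.
- A full window ends by 40 weeks (taken here as term) only if entry is by 40 − 17.4 = 22.6 weeks.
- If entry were uniform from 8 to 30 weeks (assumption), the share of full windows running past 40 weeks is (30 − 22.6)/(30 − 8) = 34%. From 12 to 30 weeks it is (30 − 22.6)/(30 − 12) = 41%.

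These shares are upper bounds on this reckoning. The window is a maximum, the questionnaire is due when the intervention is complete, and not every woman will reply.

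**3. How large is the shift?** Let p be the share of pairs with a post-birth final score and s the shift due to birth, in SDs of the change score. The documents give neither, so both are assumed. With no massage effect, the mean change is p × s and the SD is √(1 + p(1 − p)s²).

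For the number of pairs, I apply the protocol's losses to its target: 75 × 0.85 × 0.90 = 57. The rejection rate is that of a two-sided 5% paired test by normal approximation.

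| p | s | Shift p × s (SD) | Rejection rate with no massage effect, n = 57 |
|---|---|---|---|
| any | 0 | 0 | 5.0% |
| 10% | 0.5 | 0.05 | 6.6% |
| 20% | 0.5 | 0.10 | 11.5% |
| 20% | 1.0 | 0.20 | 28.9% |

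Check of the third row: SD = √(1 + 0.16 × 0.25) = 1.02, and 0.10/1.02 × √57 = 0.74. The rejection rate is Φ(0.74 − 1.96) + Φ(−0.74 − 1.96) = 0.111 + 0.003, which is 11.5% before rounding the parts.

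The Sample size section hypothesises a long-term effect below 0.1. Taking that as a standardised effect on the same scale (assumption), the second row is below the limit, the third equals it and the fourth exceeds it.

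**4. What does setting these pairs aside cost?** Confidence interval width grows by √(1/0.9) = 1.054 if 10% of pairs go and by √(1/0.8) = 1.118 if 20% go. That leaves about 51 or 46 of 57 pairs.

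**The case against.** The strongest reply is that pooling is an inference. The article does not say that post-birth finals enter the matched test, the sentence about keeping data may refer to what was gathered before birth, and a full protocol or analysis plan not shown could separate the scores. This stands as a limit on how firmly the point can be put. It does not remove it: the article goes beyond silence, since it asks for final quantitative data after birth and specifies one test on final scores.

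Four stronger readings are tempting and are not supported.
- A reader might infer that the mean change is the study's only signal. It is not. The primary outcomes are feasibility and acceptability, the four progression criteria rest on recruitment, retention, one support item and qualitative data, and MYCaW is collected at each treatment visit.
- A reader might infer that every scale is invalid after birth. Only two of the five pre-post scales are described as specific to pregnancy. The Sample size section also says that anxiety and depression stay raised until six months after delivery, which speaks against a large early fall on GAD-7. It does not cover pregnancy worry or prenatal coping.
- A reader might infer from the 47-week figure that many finals will be post-birth. It shows only that they can be. Visits are spaced by agreement and may end well before month 4.
- A reader might call the statements on ceasing and on seeking data a plain contradiction. They can be read together as stopping visit-level collection while inviting one last set, but the wording leaves that to the reader.

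There is also a fair objection to removing post-birth scores from all analyses. The Background reports a raised risk of pre-term birth in these women, so exclusion is not random and trades one bias for another. This stands, and it is why the restriction below is confined to two scales.

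**Conclusion.** The point holds in a limited form. Followed as written, the plan compares antenatal baselines with some post-birth finals in one test, and for the Cambridge Worry Score and NuPCI the two are not the same quantity. For GAD-7, PSS and SUPPH-29 the issue is possible confounding by birth, not a change of construct.

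The size cannot be determined from the documents. It is zero if birth does not shift the scores. At 20% post-birth finals and a 0.5 SD shift it reaches 0.10 SD, the upper limit of the hypothesised long-term effect. It would be wrong to say that it generally matches or exceeds that effect: 10% × 0.5 gives 0.05 SD, and both factors are assumptions. The direction is unknown.

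The outcomes are secondary and no progression decision depends on them, so this is a correction worth making and not a threat to the feasibility conclusions.

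**What to change.** - Record the completion date and pregnancy status at the final questionnaire. The team must already identify these women in order to email them.
- For the Cambridge Worry Score and NuPCI, base the pre-post test on finals completed while still pregnant, and do not send these two scales after birth.
- For GAD-7, PSS and SUPPH-29, report the pre-post change with and without post-birth finals, and tabulate the post-birth scores separately.
- Keep collecting acceptability data after birth: the post-intervention questionnaire, CARE and the interview.
- Reconcile the two adjacent statements in Data collection, for example by saying that visit-level collection stops at birth and that a named set of final instruments is still invited.

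The cost is a few lines of analysis wording, one status flag, and confidence intervals about 5–12% wider if 10–20% of pairs are set aside. The restricted results describe only women still pregnant at the final questionnaire. They under-represent early deliverers and late entrants, and the report should say so.
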